#### Secondary outcomes

The secondary outcomes are divided in health behaviors (health literacy [39], physical activity level [40], exercise self-efficacy [41], adherence to Mediterranean diet [42], and medication adherence [43]) and cardiometabolic health parameters (glycemic control [44], anthropometric characteristics, and cardiac autonomic control [45]), as described in Table 2.

**Table 2 Tab2:** Description of the secondary outcomes

Secondary outcomes	Measurement tools	Measurement description/range
Health literacy	NVS health literacy instrument	Total score ranging from 0 (no health literacy) to 6 (highest health literacy)
Physical activity level	Steps	Total steps/week and average of steps/day obtained from daily steps number for seven days measured by a pedometer
Exercise self-efficacy	Brazilian Portuguese version of BESES	Total score ranging from 0 (not confident) to 100 (completely confident)
Adherence to Mediterranean diet	Brazilian Portuguese version of the MDS	Total score ranging from 0 (no adherence) to 13 (highest adherence to Mediterranean food pattern)
Medication adherence	Brazilian version of the MAT ADOs and MAT insulin	Total score ranging from 0 (no adherence) to 7 (highest medication adherence)
Glycemic control	Results from A1c exams	Routine laboratory tests dated no longer than 3 months before the study assessment point
Anthropometric characteristics	BMI and waist circumference	Weight (kg) and height (m) measured to calculate BMI (kg/m^2^), waist circumference (cm) measured at the superior border of the iliac crest
Cardiac autonomic control	Five-minute resting HRV	SDNN (ms), RMSSD (ms), pNN50 (%), SD1 (ms), SD2 (ms), SD1/SD2 ratio, LF (ms^2^), HF (ms^2^), LF (nu), HF (nu), LF/HF ratio, TP (ms^2^)

*Abbreviations*: *NVS* Newest Vital Sign, *BESES* Bandura's Exercise Self-Efficacy Scale, *MDS* Mediterranean Diet Scale, *MAT ADOs* Brazilian version of the Measure of Adherence to Oral Antidiabetic, *MAT* insulin Insulin Treatments questionnaire, *A1c* glycated hemoglobin, *BMI* Body Mass Index, *HRV* Heart Rate Variability, *iNN* normal RR intervals, *ms* milissegundos, *SDNN* Standard deviation of iNN, *RMSSD* root mean square of the differences between successive iNN, *pNN50* percentage of successive iNN with a duration difference greater than 50ms, *SD1* Poincaré plot standard deviation perpendicular the line of identity, *SD2* Poincaré plot standard deviation along the line of identity, *LF* low-frequency spectral components, *HF* high-frequency spectral components,  *ms²* spectral components in absolute units, *nu*  spectral components in normalized units, *TP* total power

Health literacy, exercise self-efficacy, adherence to the Mediterranean diet, medication adherence, and all cardiometabolic health parameters will be measured during both the baseline and outcomes assessment appointments. Physical activity levels will be measured (1) over the 7 days following the baseline assessment appointment; (2) over the 7 days leading up to the post-intervention assessment appointment; and (3) over the 7 days following the post-follow-up assessment appointment or seven days leading up to this appointment to those participants who kept with them the pedometer worn in the past outcome assessment appointment.

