### Trial design {8}

This is a double-blinded (both outcomes’ assessors and data analysts) multicenter randomized controlled trial featuring two-arm parallel groups over 9 months (comprising a 12-week intervention period followed by a 6-month follow-up) with a 1:1 allocation ratio that follows the SPIRIT reporting guidelines [32].

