
### Participant timeline {13}

All assessment appointments will be scheduled individually, based on participants’ and research team members’ schedules.

After attending the baseline assessment appointment, the participant will be wearing a pedometer for 7 days before starting the intervention. To accommodate all participants enrolled at that time into the timetable of baseline assessment appointment and have their physical activity level measured before the intervention gets started, a period of up to 21 days including the 7-day wearing a pedometer will be allowed between the baseline assessment appointment and the first intervention session. Therefore, the baseline assessment could be carried out between one and 14 days previous to the first intervention session.

After the intervention conclusion, the participant will be wearing a pedometer for 7 days before attending the post-intervention assessment appointment. To accommodate all participants into the post-intervention assessment appointment timetable and have their physical activity level measured before this appointment, a period of up to 21 days including the 7-day wearing a pedometer will be allowed between the intervention conclusion and post-intervention assessment appointment. Therefore, the post-intervention assessment could be carried out between 7 and 21 days after the intervention conclusion.

Upon completing the 6-month follow-up, the participant will be wearing a pedometer for 7 days: (1) after attending the post-follow-up assessment appointment when this appointment is scheduled between 1 and 14 days after the 6-month follow-up completion or (2) before attending the post-follow-up assessment appointment when this appointment is scheduled between 7 and 21 days after 6-month follow-up completion. To accommodate all participants into the post-follow-up assessment appointment schedule and have their physical activity level measured after 6-month follow-up completion, a period of up to 21 days including the 7-day wearing a pedometer will be allowed between the 6-month follow-up completion and post-follow-up assessment appointment. Therefore, the post-follow-up assessment could be carried out between 1 and 14 days after the 6-month follow-up completion.

Table 3 shows the participant timeline.

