**Table 3 Tab3:**
[figure not shown]
Overview of the enrollment, interventions and assessments during the trial

t0: 1 to 21-day interval pre-intervention for the baseline assessment, t3: 1 to 21-day interval post-intervention for the post-intervention assessment, t5: 1 to 21-day interval post-follow-up for the post-follow-up assessment

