### Plans for collection, laboratory evaluation, and storage of biological specimens for genetic or molecular analysis in this trial/future use {33}

No biological specimens will be collected in this trial.

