#### Primary and secondary outcomes

Primary and secondary outcomes will be presented as central tendency and dispersion measures. Data distribution will be analyzed using the Shapiro–Wilk test. The analysis of variance (2 × 2 ANOVA) will compare data between baseline and post-intervention and between groups. An alpha of 5% will be considered for statistical significance, and post hoc comparisons will be performed to detect two-by-two differences. In case of missing data, the statistical procedures will follow the intention to treat.

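### The 3-month look-back for A1c lets a post-intervention value date from the first two weeks of the 12-week programme

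*Protocol article*

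**What the plan says.** Protocol article, Secondary outcomes, Table 2: glycemic control is measured by A1c from "Routine laboratory tests dated no longer than 3 months before the study assessment point". One look-back serves every assessment point. No rule ties the post-intervention test to the end of the programme.

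Trial design {8} sets a 12-week intervention and a 6-month follow-up. Participant timeline {13} states that "the post-intervention assessment could be carried out between 7 and 21 days after the intervention conclusion". The Table 3 footnote gives a slightly different range: "t3: 1 to 21-day interval post-intervention for the post-intervention assessment".

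The text below Table 2 adds that "all cardiometabolic health parameters will be measured during both the baseline and outcomes assessment appointments". For A1c this cannot mean a blood draw at the visit, because section {33} states: "No biological specimens will be collected in this trial". The A1c value can only be an outside result accepted under the Table 2 rule.

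The stated analysis uses this value directly: "The analysis of variance (2 × 2 ANOVA) will compare data between baseline and post-intervention and between groups".

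**The concern.** The look-back is about as long as the programme plus the minimum gap to the visit. A report from the first days of the programme can therefore be entered as the post-intervention result. Blood drawn then says nothing about the 10 to 12 weeks of exercise or education still to come, whatever one assumes about how quickly A1c responds.

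At stake is the glycaemic comparison between the combined programme and exercise alone. Each early value pulls the estimated difference towards zero, by an amount set by when routine tests happened to be ordered. A small or null A1c difference would then be hard to read, since it could reflect either no added effect or measurement too early.

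**Working it through.** The plan gives no figure of its own here, so the check is date arithmetic. Day 0 is the first session.

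**Inputs**
- Programme length: 12 weeks = 84 days (Trial design {8}).
- Gap from programme end to visit, g: 7 to 21 days (Participant timeline {13}); 1 to 21 days by the Table 3 footnote.
- Look-back, L: 3 months, taken as 91 days, with 90 and 92 as the range (Table 2).

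**Earliest acceptable post-intervention test** = 84 + g − L

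| Gap g (days) | L = 90 | L = 91 | L = 92 |
|---|---|---|---|
| 1 (Table 3 footnote) | day −5 | day −6 | day −7 |
| 7 | day 1 | day 0 | day −1 |
| 14 | day 8 | day 7 | day 6 |
| 21 | day 15 | day 14 | day 13 |

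Under the text of the timeline, the earliest acceptable test is about day 0 to 14 of 84. With the footnote's 1-day gap, it can precede the programme.

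**Six-month visit.** Taking 6 months as 182 days and a visit 1 to 21 days later, the earliest acceptable test is 182 + 1 − 91 = 92 to 182 + 21 − 91 = 112 days after the programme ends. The overlap is specific to the post-intervention visit.

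**How common early tests might be.** The documents do not say. As one illustration only, assume that test dates are spread evenly over the 91 days and gaps evenly over 7 to 21 days (mean 14):
- Test in the first 14 days: mean of (21 − g)/91 = 7/91 = 8%.
- Test in the first 7 days: mean of max(0, 14 − g)/91 = 1.75/91 = 2%.
- Test before mid-programme (day 42): mean of (49 − g)/91 = 35/91 = 38%.

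**What a tighter window would keep.** Take a window from day 70 (start of the last two weeks) to the visit. A test on day 70 follows 70/84 = 83% of the programme. The window is g + 14 = 21 to 35 days long, so under an even spread it keeps 21/91 = 23% to 35/91 = 38%, on average 28/91 = 31%. With the 100 completers per arm planned in Sample size {14}, that is about 31 per arm. If every test were taken within 21 days of the visit, all would be kept, because the earliest visit is day 91 and 91 − 21 = 70. If tests cluster early, fewer than 31% would be kept.

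**The case against.** The trial is described as pragmatic and takes no specimens, so using routine results is consistent with its design. Participants asked to bring a recent result may well bring one dated close to the visit, and assessors work from role-specific manuals that are not shown. Tests from the very first days are the tail of what the rule allows: about 2% in the first week and 8% in the first two weeks, even under an even spread. All of this stands. It limits how much dilution to expect, but it does not supply the missing date rule.

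A reader might infer three stronger things that the documents do not support.

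- **That most post-intervention values miss the intervention.** With a 91-day look-back, 77% (g = 21) to 92% (g = 7) of the acceptable window does lie before the programme ends. That share counts tests from weeks 11 and 12, which follow most of the programme and are reasonable to accept. It also describes the window, not the tests that will actually be obtained.
- **That a null A1c result would be worthless.** Dilution weakens a null result without voiding it. The 6-month A1c is free of this problem, although the stated ANOVA contrasts only baseline with post-intervention.
- **That the comparison is biased between arms.** Nothing in the protocol suggests that test timing differs by arm. Without such a difference, the effect is attenuation and added variability.

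A tighter window also has its own weakness. It selects on when a test was ordered, which may relate to clinical need after randomisation. This is a reason to show both analyses and to report test dates by arm.

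**Conclusion.** The point holds as a defect in a fixed measurement rule. A post-intervention A1c may date from about day 0 to 14 of an 84-day programme, or just before it under the Table 3 footnote. Such a value cannot reflect most of the intervention and dilutes the baseline to post-intervention contrast.

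The date limits rest only on the stated durations and on 3 months being 90 to 92 days. The amount of dilution cannot be derived, because the spread of test dates is not given; the percentages for early tests rest on an assumed even spread. A1c is a secondary outcome, so the primary outcomes and the sample size are untouched. This is a worthwhile and cheap correction, not a threat to the trial's main conclusions.

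**What to change.** Recruitment has closed and the Trial status section expects data collection to end in December 2024, so the change belongs at the analysis stage and should be fixed before the A1c data are analysed by arm.

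1. Set a date window for the post-intervention A1c tied to the end of the programme, for example from the last two weeks of the programme up to the visit. Baseline needs no new rule, since its test already precedes a visit held before the first session.
2. Report A1c test dates relative to the first session, by arm.
3. Show the A1c result under both the restricted and the current 3-month window.
4. Leave out-of-window values missing and analyse A1c with a likelihood-based repeated-measures model in place of the planned 2 × 2 ANOVA. Section {20c} would replace missing values with zero. An A1c of 0 is impossible, and applying that rule to the rejected tests would do more harm than the early tests themselves.

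**Cost.** No new blood test is needed, and the dates are already required to apply the present rule. The price is precision: about 31% of post-intervention tests kept under an even spread, more if tests cluster near the visit. The restricted estimate would be less diluted but clearly less precise, and it relies on test timing being unrelated to the unobserved A1c given the data in the model.

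### Cardiac autonomic control is twelve HRV indices with no lead index and one exact duplicate pair (RMSSD/SD1), and the planned normality check leads to no stated action

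*Protocol article*

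**What the plan says.** The protocol article, Secondary outcomes, places the measure among "cardiometabolic health parameters (glycemic control [44], anthropometric characteristics, and cardiac autonomic control [45". Table 2 gives its content as a five-minute resting HRV recording yielding "SDNN (ms), RMSSD (ms), pNN50 (%), SD1 (ms), SD2 (ms), SD1/SD2 ratio, LF (ms^2^), HF (ms^2^), LF (nu), HF (nu), LF/HF ratio, TP (ms^2". That is twelve indices, and none is marked as the one on which the outcome is judged.

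The abbreviations under Table 2 define RMSSD as "root mean square of the differences between successive iNN" and SD1 as "Poincaré plot standard deviation perpendicular the line of identity". They call nu "spectral components in normalized units" without giving the denominator.

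For analysis, Primary and secondary outcomes under Statistical methods {20a} states: "The analysis of variance (2 × 2 ANOVA) will compare data between baseline and post-intervention and between groups", and "An alpha of 5% will be considered for statistical significance". A Shapiro–Wilk test is planned, but nothing is said to follow from its result. Section {20c} replaces missing data by zero.

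The physical activity row of Table 2 has a similar feature: "Total steps/week and average of steps/day obtained from daily steps number for seven days".

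**The concern.** Twelve indices from one recording are not twelve pieces of evidence. Where one index is a fixed multiple of another, a chance difference in the first must reappear in the second, and a results table would show two significant findings that seem to support each other. With no lead index, the trial also has no rule for what counts as an effect on autonomic control, so any of the twelve could be picked out afterwards.

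A second issue is scale. LF, HF and TP in ms² and the LF/HF ratio are positive quantities and may well be right-skewed. ANOVA is the only test named, and the distribution check triggers nothing. If these indices are analysed untransformed, a real proportional change is harder to detect.

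**Working it through.** The plan gives no power or error figure for HRV, so there is none to reproduce. The inputs from the document are the twelve indices, the 5% level, and 100 completers per arm (Sample size {14}, which was set for the walk test). The treatment comparison is taken as the group-by-time term of the 2 × 2 ANOVA, which equals a t-test on change. HRV variances, correlations and skewness are not in the document and are assumed below.

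**1. Which indices are copies?**

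- *RMSSD and SD1.* With Δ the successive difference of normal intervals, SD1² = Var(Δ)/2 = (RMSSD² − mean(Δ)²)/2. Mean(Δ) is the last interval minus the first, divided by the number of differences, so it is negligible at rest. Hence SD1 = RMSSD/√2. On a simulated series, RMSSD/√2 = 20.2465 and SD1 = 20.2465. A t-test is unchanged by a constant factor, so the p-values agree. If missing values are set to 0, both become 0 and the pair stays identical.
- *LF(nu) and HF(nu).* If nu is relative to LF+HF, then HF(nu) = 100 − LF(nu), and with complete data the p-values are identical. If missing post-intervention values are set to 0 for both, the pair sums to 0 instead of 100 for those participants and the mirror breaks. In simulation with 120 per arm, HF(nu) was also significant in 100% of the cases where LF(nu) was, with nothing missing. This fell to 6.6% with 10% missing and 3.1% with 20% missing.
- *SD2, SD1/SD2, LF/HF.* These are derived but are not duplicate tests. SD2 ≈ √(2·SDNN² − SD1²), which gave 26.11 against 26.09 computed directly. LF/HF = LF(nu)/HF(nu) is a nonlinear function, and LF(nu) was significant in only 27–44% of simulated cases where untransformed LF/HF was.
- *Steps.* In a complete week, steps/week = 7 × average steps/day, so the p-values are again the same.

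**2. Chance of at least one nominally significant index under no effect**

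- Independence bound for 12 indices: 1 − 0.95^12 = 46.0%. For 10 indices (SD1 and HF(nu) removed): 1 − 0.95^10 = 40.1%.
- The indices are correlated, so the bound is too high. Null simulation of all twelve with complete data, 100 per arm and four assumed settings: 24.6% in one and 22.8% in the other three.
- Removing SD1 and HF(nu) changes none of these figures. The copies affect interpretation, not this rate.
- About 60% of the simulated trials with any significant index had two or more, with a mean of about 2.5.
- One lead index tested at 5% gives 5% by construction.

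**3. Cost of leaving skewed indices untransformed**

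Assume a log-normal index with log-SD σ, pre-post correlation ρ on the log scale, and 100 per arm. The effect giving 80% power on the log scale is

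ln(ratio) = (1.960 + 0.842) · σ · √(4(1 − ρ)/100).

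For σ = 1.0 and ρ = 0.5 this is 2.802 × 0.1414 = 0.396, a ratio of 1.486. Simulated power of the same comparison on the untransformed scale:

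| Assumed log-SD | Log scale | Untransformed |
|---|---|---|
| 0.3 | 80% | about 79% |
| 0.5 | 80% | about 75% |
| 0.8 | 80% | about 63% |
| 1.0 | 80% | about 54% |
| 1.2 | 80% | about 46% |

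Runs at ρ = 0.5 and 0.7 bracket these values: 52–57% at log-SD 1.0 and 43–48% at 1.2.

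**The case against.** The best defence is that Table 2 only describes how one outcome is measured. Multiplicity for secondary outcomes, and what follows a normality test, commonly belong to an analysis plan that is not shown. This stands in part, so neither silence is treated here as an omission in itself. It does not cover what the article fixes: twelve indices for one outcome, none leading, one duplicated, and a single named test at 5%.

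A reader might infer more than the document supports:

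- *Several indices are copies.* Under the plan as written only RMSSD/SD1 is an exact pair. LF(nu)/HF(nu) depends on a denominator the article does not give and on complete data, which the zero imputation in {20c} would undo.
- *The copies inflate the error rate.* They do not, as the simulation shows.
- *The plan commits to the untransformed scale.* It does not say so. Table 2 gives untransformed units and no transformation is named, but none is excluded.
- *Weekly steps are biased low relative to daily steps when a day is missing.* This needs an average over worn days, which the article does not define. An average over all seven days with the missing day set to zero would fall by the same proportion.

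The power figures rest on assumed skewness; at a log-SD of 0.3 the loss is about 1 point. They also ignore the removal of participants with rhythm disturbance or changed cardiovascular medication from the HRV assessment (Eligibility criteria {10}), so they illustrate the relative cost and are not forecasts. Finally, recruitment ended in February 2024, so demoting listed secondary outcomes now is a late change to be justified openly.

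**Conclusion.** The point holds in limited form. RMSSD and SD1 are one measurement listed as two outcomes. LF(nu) and HF(nu) are too, given complete data and LF+HF normalisation, as are the two steps measures in a complete week. The harm from copies is false corroboration.

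The missing lead index is the larger matter. It leaves roughly a 23–25% chance of at least one nominally significant HRV index when there is no effect, under an assumed correlation structure and complete data. The loss of power from an untransformed analysis is conditional on that scale being used and on right skew: from about 1 point at an assumed log-SD of 0.3 to about 34 points (80% − 46%) at 1.2.

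Severity is low to moderate. Only secondary outcomes are touched, and the conclusions on walking distance and knowledge are unaffected.

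**What to change.** Before data lock, decided by people blinded to allocation:

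- In Table 2, name one lead HRV index for cardiac autonomic control, for example ln RMSSD, and judge the outcome on it.
- Report SD1 and one of LF(nu)/HF(nu) without separate tests, and state the denominator of the normalised units.
- Label the remaining indices supportive or descriptive.
- Analyse LF, HF, TP and LF/HF after natural-log transformation and report ratios of geometric means. Fix this in advance and do not let Shapiro–Wilk decide it.
- Exempt HRV from the zero imputation in {20c}. The log of 0 is undefined, so the log analysis cannot run while that rule applies.
- Test only one steps measure.

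The cost is wording in Table 2 and the statistical section, with no new data. The downsides are that fewer HRV indices can be claimed as outcomes, and that the change must be documented, with its date and reason, as a late amendment.

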#### Tertiary outcomes

The tertiary outcomes included in this study will be program adherence, satisfaction with the program, diabetes-related morbidity, quality of life, depression, and diet quality.Program adherence will be measured by the attendance rate in the program for each participant. The attendance rate of participants in the on-site delivery mode will be calculated based on the number of education classes and/or exercise sessions attended, divided by the total number of education classes and/or exercise sessions offered. For participants in the remote delivery mode, the attendance rate will be determined by the number of weeks exercise and /or study diaries were filled out, divided by the program’s duration in weeks.Satisfaction with the program will be measured by questionnaires developed by the researchers. For participants in the on-site delivery mode, the level of satisfaction with the patient education program will be assessed by an 11-item questionnaire, and with the exercise program by a 4-item questionnaire. For participants in the remote delivery mode, the level of satisfaction with the patient education program will be assessed by a ten-item questionnaire and with the exercise program by a five-item questionnaire.Diabetes-related morbidity will be assessed through the number and description of acute complications and diagnoses of chronic complications of diabetes, along with the number of hospitalizations associated with diabetes. The information will be collected using a three-item tool during the 6-month follow-up period.Quality of life will be evaluated using the Medical Outcomes Study 36-Item Short-Form Health Survey (SF-36) [46]. The total scores range from 0 (indicating no quality of life) to 100 (indicating the highest quality of life). This is obtained through a 36-item tool distributed across various physical and mental health domains, including physical functioning, social functioning, role–physical, bodily pain, mental health, role–emotional, vitality, and general health.Depression will be measured by the Brazilian version of the Center for Epidemiological Scale—Depression (CESD) [47]. The total score ranges from 0 (indicating no depressive symptoms) to 60 (indicating the highest level of depressive symptoms). This is obtained through a 20-item tool used to rate how often the interviewed experienced symptoms associated with depression over the past week, such as restless sleep, poor appetite, and feeling lonely. Response options range from 0 to 3 for each item (0 = rarely or none of the time, 1 = some or little of the time, 2 = moderately or much of the time, 3 = most or almost all the time).Diet quality will be measured through the consumption of macro and micronutrients. Food consumption will be assessed using an adapted version of a validated Food Frequency Questionnaire (FFQ) for Brazilian individuals with type 2 diabetes [48, 49], evaluating consumption frequency (daily, weekly, monthly, or yearly), number of portions, and serving size (small, medium, large or extra large). The adaptation of the FFQ was necessary since the individuals in this research have different eating habits than in the validated FFQ study, so regional adaptations were necessary. This adaptation was made based on a food diary on three non-consecutive days, including a weekend day carried out with 65 volunteers with type 1 or type 2 diabetes [42]. The final FFQ consists of 104 food items distributed across eight food groups (“cereals, tubers, roots, and derivatives”; “vegetables and legumes”; “fruits”; “beans”; “meat and eggs”; “milk and dairy products”; “oils and fats”; “sugars and sweets”), as well as 11 items investigating beverages, 4 items investigating oilseeds, and 1 item investigating food supplement.
